## Abstract

**Background:**

Nasal continuous positive airway pressure (CPAP) applies positive end-expiratory pressure (PEEP) and has been shown to reduce the need for intubation and invasive mechanical ventilation in very low birth weight infants with respiratory distress syndrome. However, CPAP failure rates of 50% are reported in large randomized controlled trials. A possible explanation for these failure rates is the application of insufficient low levels of PEEP during nasal CPAP treatment to maintain adequate functional residual capacity shortly after birth. The optimum PEEP level to treat symptoms of respiratory distress in very low birth weight infants has not been assessed in clinical studies. The aim of the study is to compare two different PEEP levels during nasal CPAP treatment in preterm infants.

**Methods:**

In this randomized multicenter trial, 216 preterm infants born at 26 + 0–29 + 6 gestational weeks will be allocated to receive a higher (6–8 cmH_2_O) or a lower (3–5 cmH_2_O) PEEP during neonatal resuscitation and the first 120 h of life. The PEEP level within each group will be titrated throughout the intervention based on the FiO_2_ (fraction of inspired oxygen concentration) requirements to keep oxygenation within the target range. The primary outcome is defined as the need for intubation and mechanical ventilation for > 1 h or being not ventilated but reaching one of the two pre-defined CPAP failure criteria (FiO_2_ > 0.5 for > 1 h or pCO_2_ ≥ 70 mmHg in two consecutive blood gas analyses at least 2 h apart).

**Discussion:**

Based on available data from the literature, the optimum level of PEEP that most effectively treats respiratory distress syndrome in preterm infants is unknown, since the majority of large clinical trials applied a wide range of PEEP levels (4–8 cmH_2_O). The rationale for our study hypothesis is that the early application of a higher PEEP level will more effectively counteract the collapsing properties of the immature and surfactant-deficient lungs and that the level of inspired oxygen may serve as a surrogate marker to guide PEEP titration. Finding the optimum noninvasive continuous distending pressure during early nasal CPAP is required to improve CPAP efficacy and as a consequence to reduce the exposure to ventilator-induced lung injury and the incidence of chronic lung disease in this vulnerable population of very preterm infants.

**Trial registration:**

drks.de DRKS00019940. Registered on March 13, 2020

## Introduction

### Background and rationale {6a}

Very low birth weight infants (VLBWI) with surfactant deficient lungs frequently develop respiratory distress syndrome (RDS) with the need of early respiratory support in the delivery room and during the active phase of RDS (i.e., first 5 days of life) [1]. The use of nasal CPAP to avoid intubation and the consecutive detrimental effects of invasive mechanical ventilation to the immature lungs has been shown to reduce the rate of bronchopulmonary dysplasia (BPD) and death in meta-analyses [2]. The diagnosis of BPD is associated with lifelong impaired lung function and negatively affects the neurodevelopmental outcome in this high risk group of infants [3]. Nasal CPAP in the delivery room is now the recommended primary respiratory support in preterm infants with RDS. Results of large randomized controlled trials comparing early nasal CPAP versus primary intubation found that approximately 46.0–51.2% of infants can be saved from intubation with this approach [4, 5]. However, almost half of the infants in the large CPAP trials failed on CPAP, which ultimately resulted in exposure to some degree of invasive mechanical ventilation and may explain limited effects on the reduction of the incidence of BPD [1, 6, 7]. Application of early nasal CPAP aims to recruit the lungs and maintain functional residual capacity (FRC). The degree of lung recruitment is influenced by the level of PEEP applied to the immature lung [8]. Expert panels from international societies currently recommend a PEEP level of 5–6 cmH_2_O [4, 9]. However, as the authors state, evidence for these recommendations is very limited. No clinical studies specifically assessed the effect of different PEEP levels during the active phase of RDS in preterm infants on outcomes such as the need for invasive mechanical ventilation and other neonatal morbidities (i.e., BPD). Results of a secondary analysis from a cohort study in 34 international centers that participated in a nasal intermittent positive pressure ventilation trial indicate a large variation of PEEP levels used in clinical practice during neonatal resuscitation and the first 28 days of life (i.e., 3–9 cmH_2_O) [10]. Only one clinical trial with a small sample size, including preterm infants beyond the active phase of RDS, randomized subjects to receive a higher or a lower level of PEEP after extubation (4–6 cmH_2_O versus 7–9 cmH_2_O) and found a significantly lower rate of reintubation in the higher PEEP group [11]. Results from animal studies further suggest that using higher PEEP levels (8–12 cmH_2_O) improves gas exchange and avoids lung collapse when compared to lower levels of PEEP [12, 13]. The optimum level of PEEP during nasal CPAP that effectively maintains FRC and avoids mechanical ventilation in preterm infants with RDS is unknown and remains to be determined.

The proposed randomized controlled trial was designed and powered to compare the effect of two different PEEP levels during nasal CPAP (6–8 cmH_2_O versus 3–5 cmH_2_O) in preterm infants in the first 120 h of life on the need for intubation and the incidence of pre-defined CPAP failure criteria.

### Objectives {7}

The primary hypothesis of this study is that the use of a higher PEEP range in preterm infants born at 26 + 0–29 + 6 weeks gestational age (GA) receiving prophylactic nasal CPAP support after birth reduces the incidence of intubation and/or meeting predefined CPAP failure criteria within the first 120 h of life when compared to the application of a lower PEEP range.

### Trial design {8}

This will be an unblinded multicenter randomized controlled parallel group comparison of two different PEEP ranges during nasal CPAP support in the first 120 h of life.

### Eligibility criteria {10}

#### Inclusion criteria

GA at birth 26 + 0/7 to 29 + 6/7 weeks

#### Exclusion criteria

Severe congenital anomalies affecting breathing control (cerebral anomalies, chromosomal anomalies, prenatally diagnosed intracranial hemorrhage) *or* gas exchange (pulmonary hypoplasia due to congenital diaphragmatic hernia or oligo/anhydramnios present at < 22 weeks GA or other pulmonary or intrathoracic malformations, etc.) *or* hemodynamics (cyanotic heart disease, ductal dependent systemic perfusion, or similar)Decision not to provide full life support/decision for palliative care only before study entryParents not able to understand the study due to language barriers

### Who will take informed consent? {26a}

All pregnant women who are admitted to the local prenatal/maternity wards with threatening preterm delivery before 29 + 6/7 weeks should be approached. Both parents will be asked for consent for their baby to participate in the study given that it will be delivered between 26 + 0 and 29 + 6 weeks of gestation. Informed consent will be taken by good clinical practice (GCP) qualified staff members.

### Additional consent provisions for collection and use of participant data and biological specimens {26b}

To date, no sampling of biological material is planned during the study.

## Interventions

### Explanation for the choice of comparators {6b}

Since the optimum level of PEEP to treat RDS is unknown, we decided to choose the levels of PEEP within the reported PEEP levels used in clinical practice from large surveillance data (3–9 cmH_2_O) and within the limits of current treatment guidelines [4, 9, 10]. To allow for effective discrimination between the two treatment groups, we decided that the difference of the applied level of PEEP in the delivery room must be exactly 3 cmH_2_O. At last, the choice of the defined PEEP levels yielded the highest agreement in the pre-study meetings of all participating centers.

### Intervention description {11a}

#### Study intervention

The study intervention is the application of early nasal CPAP/nasal intermittent positive pressure ventilation (NIPPV) with higher PEEP range (6–8 cmH_2_O, intervention group) compared to a lower PEEP range (3–5 cmH_2_O, control group) in the first 120 h of life.

#### Interventional period

The intervention starts immediately after birth with the first application of nasal CPAP/NIPPV in the delivery room. The study intervention ends at a postnatal age of 120 h. Randomized subjects will receive nasal CPAP/NIPPV immediately after birth using a short nasopharyngeal tube, face mask, or binasal prongs (center specific). The PEEP level will be set within the allocated PEEP range: PEEP_low_ (3–5 cmH_2_O) or PEEP_high_ (6–8 cmH_2_O). During resuscitation, the *initial* PEEP setting in the intervention group must be set 3 cmH_2_O higher than in the control group and will be determined by center guideline prior to study start. The initial PEEP will be *maintained* during the delivery room management and will not be adjusted. Application of PEEP in the delivery room will be provided by a T-Piece resuscitator or a conventional ventilator. The use of a self or flow-inflating bag is not permitted for initial respiratory support. Subjects will be further resuscitated according to the European Consensus Guidelines [4]. Sustained inflation maneuvers can be applied according to local policies for initial stabilization. Primary nasal NIPPV (synchronized or not) can be used in the delivery room. After admission to the neonatal intensive care unit, the PEEP level will be adjusted according to the level of inspired oxygen required to meet the center-specific study SpO_2_ target range within the maximum range of 85–95% throughout the interventional period using the following PEEP titration protocol: (PEEP adjustments should be made on a half-hourly basis to allow the assessment of effects).

Prior to study initiation, we strongly recommend local guidelines for intubation and mechanical ventilation be defined, as well as the indication criteria for surfactant administration that have to be applied equally within both PEEP groups. Suggested intubation criteria within the study are:

FiO_2_ ≥ 0.5 for > 1 h and/or pCO_2_ ≥ 70 mmHg in two consecutive blood gas analysis > 2 h apart after the application of a maximum of 2 surfactant doses (either INSURE (intubate surfactant extubate) or less invasive, i.e., LISA).

If a study subject requires intubation, decisions on the mode of invasive ventilation, weaning strategies, and extubation are at the discretion of the responsible medical team of the study site with settings and modes identical for both treatment groups. After extubation, the PEEP will be set and adjusted according to the initially assigned PEEP range during nasal CPAP/NIPPV. After the study intervention period, the medical team at each study site will decide on the further mode of respiratory support and weaning strategies.

#### Continuous documentation of the study intervention

In both treatment groups, FiO_2_, set PEEP levels, and pressures during CPAP and NIPPV (mean airway pressure, peak inspiratory pressure, inspiratory time) will be recorded every hour throughout the interventional period on a worksheet and has to be signed by a study physician. All data will be transferred from hardcopy to electronic CRF files and are stored within the database of the center for pediatric clinical studies (CPCS), University of Tuebingen. This database fulfills all GCP and FDA CFR part 11 requirements. After termination of the study, all datasets are backed up within a locked area at the Justus-Liebig-University of Giessen and at the Eberhard-Karls-University of Tuebingen for at least 10 years after the end of the study.

### Criteria for discontinuing or modifying allocated interventions {11b}

#### Individual preterm end of study intervention

##### For the individual patient

Treatment may be terminated for safety concerns by the attending physician together with the local principal investigator or according to the wish of the patient’s parents or legal representatives at any time. The reasons for premature termination of the study intervention have to be documented in the study database. These patients will be maintained in the study, study visits have to be done as planned, and their outcome will be included in the intention-to-treat analysis.

#### Preterm end of study

##### For a study center

A study center not following the protocol or failing to recruit patients may be closed prematurely. All infants already recruited at that center will be maintained in the study, study visits have to be done as planned, and their outcome will be included in the intention-to-treat analysis.

##### For the whole study

For safety: all potential complications related to the intervention occurring during the care of an infant enrolled in this trial have to be reported immediately to the coordinating investigator according to ICH-GCP guidelines and national and European regulations. Furthermore, information on all prematurity-associated complications is collected in the study database. These will include safety reports after 50, 100, and 150 completely documented patients to the data monitoring committee (DMC), who will continuously keep track of the incidence of such events in both study groups. The trial will be stopped by the coordinating investigator on the advice of the DMC, if the risk-benefit ratio of the study intervention (i.e., application of higher PEEP ranges) is significantly changed based on new published data becoming available. The trial will also be stopped temporarily or permanently in case that safety outcomes (i.e., mortality or major diseases of prematurity) occur more frequently in the treatment group or if complications directly related to the study intervention (e.g., adverse events directly attributable to device failures) require a change in the risk-benefit assessment.

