### Composition of the data monitoring committee, its role and reporting structure {21a}

The DMC is represented by two neonatologists independent from the sponsor or competing interests. The DMC will be contacted by the two coordinating investigators ([name] and [name]) based on their expertise (being at least principal investigators in clinical trials for more than 5 years in the past and experts in the field of neonatology). Details (name and contact information) of the composition of the DMC are provided in the study protocol or upon request. Safety aspects will be documented continuously throughout the study including the categories expected serious adverse events (eSAE) and unexpected serious adverse events (uSAE) events and will be reported within safety reports to the DMC. Safety analyses will be done after 50, 100, and 150 included patients have reached PMA 36 weeks. Reports of these data will be sent to the DMC members by the responsible biometrician (CPCS, University of Tuebingen). Based on the reported data, the DMC will provide recommendations on continuation of the trial and will report its decision to the coordinating investigators.

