### Adverse event reporting and harms {22}

The following expected serious (eSAE) and unexpected serious (uSAE) adverse events known to occur in this population of very preterm infants will be reported to the DMC as rates and percent, stratified for treatment group.

*eSAE:*
Death before dischargeNecrotizing enterocolitis stage ≥ 2 or need for surgeryFocal intestinal perforationAny intraventricular hemorrhageAny intraventricular hemorrhage ≥ 3°Periventricular leucomalaciaAny persistent ductus arteriosus requiring treatment (medical/surgical)Any retinopathy of prematurity requiring treatmentRate of air leak syndromes (i.e., pneumothorax, pulmonary interstitial emphysema, pneumoperitoneum, pneumopericardium, pneumomediastinum)Rate of any air leak syndrome associated with any intraventricular hemorrhage

All other adverse events meeting the following criteria of seriousness will be considered unexpected serious adverse events and must be documented in the AE-from of the eCRF.

*uSAE* (any adverse event that resulted in any of the following):
DeathSerious deterioration in the health of the subject that resulted in any of the following:
Life-threatening illness or injury,Permanent impairment of a body structure or a body function,Medical or surgical intervention to prevent life-threatening illness or injury or permanent impairment to a body structure or a body function.

To ensure that there is no higher risk of deaths caused by the intervention, this will be evaluated with the help of 95% confidence limits that will be presented for both treatment groups. A DMC manual will describe the details of the safety analysis and has to be approved by all DMC members before preparing the first DMC report.

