## Discussion

Nasal CPAP application with selective surfactant administration is currently the primary and recommended respiratory support in very low birth weight infants with developing or active RDS [1, 4]. CPAP has been proven to be at least as effective as primary intubation in the delivery room with regard to the outcome of BPD and significantly reduced the need for invasive mechanical ventilation in large randomized controlled trials [1, 6, 7]. However, reported CPAP failure rates in these trials are still high (46.0–51.2%) and CPAP failure was ultimately linked with the exposure to mechanical ventilation, an intervention clearly associated with the diagnosis of BPD [5, 14, 16]. PEEP levels used in these trials ranged from 4 to 8 cmH_2_O. The evidence for the decision to apply these specific PEEP levels of 4–8 cmH_2_O in very immature preterm infants is low but considered to be safe. From a pathophysiological perspective, early application of PEEP to the surfactant deficient lungs counteracts the collapsing properties, maintains FRC, and supports lung liquid clearance immediately after birth [17]. In an attempt to accelerate lung liquid clearance, sustained increases of continuous positive airway pressure (i.e., sustained lung inflation maneuvers (SLI)) have been proposed to effectively recruit gas exchange units after birth [18]. While this SLI strategy has been shown to reduce the need for intubation within the first 72 h of life in VLBWI, the results of the SAIL trial showed no difference in the rate of BPD, but an increased mortality in the SLI group discouraging the use of this aggressive recruitment technique [18, 19]. Effective lung liquid clearance is necessary to allow gas exchange, but the approach of SLI does not take into account the fact that interstitial liquid tends to re-accumulate in the pulmonary tissue over a longer period of time [20]. In addition, RDS caused by primary surfactant deficiency of the premature lungs predisposes atelectasis and consecutive impaired gas exchange. It is considered a longer lasting dynamic disease process and therefore may require prolonged and sufficient PEEP support [21]. Early surfactant treatment, in the recent years predominantly administered via less invasive application procedures or the INSURE technique in the neonatal population, further reduced the need of invasive ventilation, but unfortunately did not yield the desired reduction in the incidence of BPD in multicenter studies [7, 14]. Stepwise recruitment strategies (IN-REC-SUR-E – Intubate Recruit Surfactant Extubate) using invasive high frequency oscillatory ventilation, where FiO_2_ serves as surrogate marker of effective lung inflation, combined with surfactant administration are currently under investigation and have been shown to reduce oxygen requirements and the incidence of BPD in one randomized controlled trial and retrospective studies [15, 22, 23]. SLI maneuvers and the INRECSURE procedures aim to apply higher pressures over a short period of time indicating that the immature preterm lung may require higher continuous distending pressures than expected in the past. However, clinical trials assessing the application of early, prolonged and higher levels of non-invasive PEEP to avoid collapse of the neonatal lung during nasal CPAP are not available but may be an alternative or adjunctant to the abovementioned ventilation and treatment strategies. The hypothesis that early application of “higher” PEEP levels could be beneficial is supported by animal data where higher PEEP levels (8–12 cmH_2_O) were more effective than lower levels in terms of gas exchange [12, 13]. More recently, a dynamic increase of PEEP in preterm lambs (up to 14–20 cmH_2_O for 3 min) improved response to surfactant treatment and created a more uniform lung aeration, compared to positive pressure ventilation or SLI maneuvers [24]. Further evidence that higher pressure levels may decrease the need for invasive mechanical ventilation derives from studies using NIPPV as a mode of non-invasive respiratory support. This ventilation strategy augments CPAP by superimposing positive pressure inflation at different respiratory rates, imitating time-cycled pressure-controlled ventilation. Results of the actual meta-analyses showed a reduction of the need for intubation and reintubation compared to nasal CPAP when NIPPV was used as primary mode of ventilation or post extubation [25, 26]. It is unclear how NIPPV mediates its clinical benefits, but one possible explanation could be the increase in mean airway pressure during NIPPV [27].

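### The only between-arm stopping criterion on the trial's own data is written for an excess in the higher-PEEP group alone, and on raw frequencies

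*Protocol article*

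**What the plan says.** All references are to the protocol article.

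- **Criteria for discontinuing {11b}, For the whole study.** The section gives three grounds for stopping: newly published data that change the risk-benefit ratio; safety outcomes that differ between the arms; and complications directly related to the intervention, such as device failure. Only the second compares the arms on the trial's own data. It applies "in case that safety outcomes (i.e., mortality or major diseases of prematurity) occur more frequently in the treatment group". The same section explains the study intervention as the application of higher PEEP ranges, so the treatment group here is the 6–8 cmH2O arm. The section also has the DMC "continuously keep track of the incidence of such events in both study groups".
- **Adverse event reporting and harms {22}.** The mortality check has the aim "To ensure that there is no higher risk of deaths caused by the intervention" and uses "95% confidence limits that will be presented for both treatment groups". Details are left to a DMC manual, which is not shown.
- **Composition of the data monitoring committee {21a}.** After the reports at 50, 100 and 150 infants, "the DMC will provide recommendations on continuation of the trial". No direction is attached.
- **Study intervention {11a}.** The comparator is the "lower PEEP range (3–5 cmH_2_O, control group) in the first 120 h of life".
- **Background and rationale {6a}** reports 5–6 cmH2O as the level recommended by expert panels and calls the evidence for it very limited. **The Discussion** says that the evidence for "these specific PEEP levels of 4–8 cmH_2_O in very immature preterm infants is low but considered to be safe".

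**The concern.** A harm criterion in one direction is natural when the control arm is established care and only the new treatment carries unknown risk. By the article's own figures, that is not quite the position here. Much of the 3–5 cmH2O range lies below the recommended level, and its lower end lies below the levels described as considered safe. The trial's hypothesis is that low PEEP leads to more treatment failure, and the Discussion links CPAP failure to mechanical ventilation and ventilation to BPD. Excess morbidity in the lower arm is therefore plausible.

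If it occurred, the protocol would attach no consequence to it, while the same excess in the other arm would call for a stop. What is at stake is equal written protection for infants in both arms, and a criterion the DMC can apply.

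The wording has a second weakness: more frequent, with no margin, is met by a single extra event.

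**Working it through.** **1. Ranges set side by side (cmH2O)**

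| Reference | Range | Control 3–5 | Intervention 6–8 |
|---|---|---|---|
| Recommended, {6a} | 5–6 | only 5 inside; 3 to <5 below | only 6 inside; >6 to 8 above |
| Considered safe, Discussion | 4–8 | 3 to <4 below | wholly inside |

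Both arms leave the recommended range, one on each side. Only the control arm leaves the 4–8 range.

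**2. Direction of each safety provision**

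| Provision | Direction |
|---|---|
| Stopping criterion on safety outcomes, {11b} | higher-PEEP excess only |
| Published-data ground, {11b} | none |
| Related complications, {11b} | not a between-arm comparison |
| DMC tracking of events, {11b} | both groups |
| DMC recommendation on continuation, {21a} | none |
| Mortality check, {22}: stated aim | intervention only |
| Mortality check, {22}: limits shown | both groups |

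The asymmetry therefore lies in one criterion and one stated aim.

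**3. How the raw-frequency wording behaves**

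Inputs: 1:1 allocation (Sequence generation {16a}) and reports at 50, 100 and 150 infants ({21a}), taken as 25, 50 and 75 per arm. The article gives no mortality rate, so 3%, 5%, 10% and 20% are assumptions.

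Let X_H and X_L be the deaths in the high and low arms, independent binomials with n = 75. Then P(X_H > X_L) = Σ over h > l of P(X_H = h)·P(X_L = l). With equal rates, P(X_L > X_H) is the same. The three-report figures come from 400,000 simulated trials with cumulative counts.

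| Mortality, both arms | High arm has more deaths, 150-infant report | High arm has more deaths, at least one of three reports |
|---|---|---|
| 3% | 40.2% | 53.5% |
| 5% | 42.4% | 57.7% |
| 10% | 44.5% | 61.1% |
| 20% | 45.9% | 63.1% |

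Read literally, the criterion is met on deaths alone in roughly two of five final reports when PEEP has no effect on mortality.

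If mortality is truly doubled in the low arm (6 vs 3%, 10 vs 5%, 20 vs 10%), the low arm has more deaths in 76%, 85% and 95% of 150-infant reports. The written criterion covers none of these.

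**4. An either-direction criterion with a margin**

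Illustrative margin: the 95% interval for the risk difference d = p_L − p_H excludes 0. With Wilson limits (l, u) for each arm, the Newcombe lower limit is d − √[(p_L − l_L)² + (u_H − p_H)²]; the upper limit is analogous.

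| True mortality, low vs high | Low arm flagged, 150-infant report | Low arm flagged, any of three reports |
|---|---|---|
| 3 vs 3% | 1.0% | 1.1% |
| 5 vs 5% | 1.7% | 2.3% |
| 10 vs 10% | 2.4% | 4.2% |
| 20 vs 20% | 2.4% | 5.4% |
| 6 vs 3% | 9.9% | 11.6% |
| 10 vs 5% | 19% | 23% |
| 20 vs 10% | 40% | 46% |
| 30 vs 10% | 88% | 90% |

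With equal rates, a false signal in either direction over the three reports has probability 2.3%, 4.7%, 8.3% and 10.7%.

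**The case against.** The strongest reply is that low-arm harm is already covered. The DMC sees both arms and may recommend stopping for either, and its manual, to be approved before the first report, may contain a two-sided rule. The hypothesis is directional and higher PEEP is the experimental treatment, so an explicit trigger for that arm alone is a defensible choice. Most of this stands, and it is why the point is minor. It does not remove the point: the direction is something the protocol states, not a detail left to the manual, and the manual should not have to override a protocol criterion.

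Stronger readings that the article does not support:

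- *Harm in the low arm goes unmonitored.* It does not: tracking, reports and confidence limits all cover both arms.
- *The mortality check looks only at the higher-PEEP arm.* Only its stated aim is directional.
- *The article implies that 3 cmH2O is unsafe.* The 4–8 range describes levels used in earlier trials and sets no floor. PEEP is also titrated to oxygen need after NICU admission.
- *The control range breaches guidelines.* Explanation for the choice of comparators {6b} says that the levels lie within reported practice (3–9 cmH2O) and within guideline limits. The guidelines are not at hand, so this cannot be checked.

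A further fair objection is that a margin has little power. Even the risk-difference interval misses most doublings of mortality. Non-overlap of the separate limits for each arm would be weaker still: at 75 per arm it flags the three doublings in about 1%, 4% and 13% of reports, and 30 vs 10% in about 63%. That is a reason to use the interval for the difference and to leave the decision to DMC judgement.

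**Conclusion.** The point holds as a minor one. The only between-arm stopping criterion on the trial's own data runs in one direction, and a materially higher rate of death or major morbidity in the 3–5 cmH2O group has no written consequence. As worded, the criterion is also unusable as a rule: with no true difference it is met on deaths alone in 40–46% of 150-infant reports, and at least once over three reports in about 53–63%.

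These figures rest on an assumed mortality of 3–20%, equal arm sizes at each report, independent infants, and a literal reading of more frequently. They do not predict that the trial would be stopped that often, since the DMC would exercise judgement and its manual is not shown. The primary analysis, its type I error and its power are unaffected.

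**What to change.** - **For the whole study {11b}:** state that the trial will be stopped temporarily or permanently, on the advice of the DMC, if mortality or major morbidity is materially higher in either PEEP group, judged on the 95% confidence interval for the between-group risk difference. Put the margin in the DMC manual.
- **Adverse event reporting and harms {22}:** state the aim as assessing whether the risk of death is higher in either group.
- **DMC manual:** add a matching line, and show the interval for the difference beside the limits for each group.

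The cost is two wording edits and one line in the manual. The planned reports already hold both arms' data, so nothing new is collected, and the primary outcome is not tested there.

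There are two downsides. The trial could be stopped on a false low-arm signal; under the illustrative margin its probability over three reports is about 1–5%, and the DMC still decides. And for the higher-PEEP arm, a commitment that reads as automatic on raw frequencies becomes a DMC judgement. That is a real softening, accepted because the raw trigger is met by chance so often.

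### The whole-trial stopping condition makes no allowance for chance, and the mortality check gives confidence limits per group, not for the difference between groups

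*Protocol article*

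**What the plan says.** All references are to the protocol article.

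- **Criteria for discontinuing {11b}, For the whole study.** The sentence opens "The trial will also be stopped temporarily or permanently in case that". Its first condition is that "safety outcomes (i.e., mortality or major diseases of prematurity) occur more frequently in the treatment group". Its second concerns complications directly related to the intervention that "require a change in the risk-benefit assessment". The sentence before it, on newly published data, makes stopping depend on DMC advice and on a significant change in the risk-benefit ratio. The safety sentence does not repeat either condition.
- **Composition of the data monitoring committee {21a}.** "Safety analyses will be done after 50, 100, and 150 included patients have reached PMA 36 weeks". From these reports "the DMC will provide recommendations on continuation of the trial".
- **Adverse event reporting and harms {22}.** Ten categories of expected serious adverse event are listed, some of them nested. These "will be reported to the DMC as rates and percent, stratified for treatment group". On whether the intervention raises the risk of death, "this will be evaluated with the help of 95% confidence limits that will be presented for both treatment groups". Finally, "A DMC manual will describe the details of the safety analysis", and all DMC members must approve that manual before the first report is prepared.

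**The concern.** With 1:1 allocation and no true effect, one group will usually have more events than the other, and about half of those imbalances will be against the higher-PEEP group. A condition met by any excess is therefore often met by chance. It is met more often when it is checked three times and over several outcomes. At stake is a halt of a 216-infant trial for no reason, or a DMC that must set the protocol's wording aside in order to continue.

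The mortality evaluation has a different weakness. The question is comparative, but two single-group intervals do not estimate a difference. The two sections also give unconnected criteria for the same outcome: one responds to any excess, and the other calls for a measure of uncertainty.

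**Working it through.** **Inputs from the document.** Looks at 50, 100 and 150 infants, allocation 1:1, so about 25, 50 and 75 per group. The document states no operating figure for the safety rule, so there is none to reproduce.

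**Assumed inputs.** Event rates and correlations, shown as ranges because the document gives none.

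**1. Excess deaths at a single look, no true difference.** With T and C the deaths in the higher- and lower-PEEP groups, both binomial with the same n and p, symmetry gives P(T > C) = [1 − P(T = C)] / 2.

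| Assumed mortality | 25 per group | 50 per group | 75 per group |
|---|---|---|---|
| 3% | 0.316 | 0.378 | 0.402 |
| 5% | 0.364 | 0.406 | 0.424 |
| 10% | 0.405 | 0.433 | 0.445 |

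**2. Excess deaths at one or more of the three looks.** Deaths accumulate by 25 infants per group between looks, and a trial counts once T > C at any look. The results are 53% at 3% mortality, 58% at 5% and 61% at 10%.

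**3. Any one of several outcomes.** With independent outcomes at 5% each, 0.576 is the probability for one outcome over three looks.

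- Three outcomes: 1 − (1 − 0.576)³ = 1 − 0.076 = 0.924.
- Four outcomes: 1 − (1 − 0.576)⁴ = 1 − 0.032 = 0.968.

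Outcomes in the same infant are correlated, which lowers these figures. In a simulation with assumed rates of 2-35% and a latent within-infant correlation of 0 to 0.6, the condition was met by the third look in 92-97% of trials for four outcomes and 97-99.9% for eight.

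**4. Per-group limits against an interval for the difference.** The document does not say how the per-group limits are to be read. Suppose harm were declared only when the two 95% intervals do not overlap. With equal standard errors, the estimates must then differ by 2 × 1.96 SE. The standard error of the difference is √2 SE, so z = 2 × 1.96 / √2 = 2.77, or two-sided p of about 0.006.

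The table gives the exact probability of flagging excess deaths at the largest planned look (75 per group), one look at a time:

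| True mortality, lower vs higher PEEP | Non-overlap, Clopper-Pearson | Non-overlap, Wilson | 95% CI for the difference (Newcombe) excludes 0 |
|---|---|---|---|
| 5% vs 5% | <0.1% | 0.1% | 1.7% |
| 5% vs 10% | 2.5% | 4.3% | 19% |
| 5% vs 15% | 17% | 22% | 54% |
| 10% vs 20% | 10% | 13% | 40% |

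As an example in counts, against 3 deaths among 75 infants, non-overlap of Clopper-Pearson limits needs 15 deaths in the other group. Fisher's exact test reaches p < 0.05 at 11.

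**The case against.** The strongest reply is that the protocol describes no automatic trigger. The stop may be temporary, the DMC recommends on continuation from the reported data, and the risk-benefit wording that ends the sentence could be read as covering both of its conditions. The details of the safety analysis are assigned to a DMC manual that is not shown, and a journal article need not repeat them. Safety monitoring also does not enter the confirmatory analysis.

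Much of this softens the point, but it does not remove it. The first condition has its own verb and is complete without the risk-benefit phrase, and the sentence is mandatory in form. The issue is a criterion that the article does state, not detail that it leaves out.

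Three stronger readings are tempting, and the document does not support them:

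- **That the stopping rule would almost always fire without harm.** This needs any one of several outcomes to be enough. The sentence names mortality and major diseases of prematurity but gives no list and no counting rule. For deaths alone the figure is 53-61%.
- **That the mortality evaluation will miss real harm.** This needs non-overlap to be the decision rule, and the harms section does not say so. Small numbers are also part of the problem: at 75 per group the interval for the difference itself misses about 81% of true doublings from 5% to 10% (100% − 19%).
- **That the DMC manual could only help by contradicting the protocol.** It could add an interval for the difference beside the per-group limits without conflict. It could also say how an excess is judged, although a threshold there would sit awkwardly with a mandatory sentence that has none.

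**Conclusion.** The point holds in limited form. The stopping sentence fixes a condition that, taken as written, chance alone would meet in more than half of harmless trials on deaths alone. If any one of three independent 5% outcomes is enough, that rises to about 92%. These figures rest on assumed event rates, on about 25 infants per group being added at each look and, for three outcomes, on independence. Correlation lowers the multi-outcome figures but leaves them high.

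The harms section names the wrong quantity for its own question. What this costs depends on how the limits are read. Under a non-overlap reading, which is possible but not stated, a true 5% vs 15% would be flagged at 75 per group in about 17% of trials (Clopper-Pearson), against 54% with an interval for the difference. For 5% vs 10% the figures are 2.5% and 19%, so neither method is sensitive at this size.

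The stopping sentence, the DMC's advisory role and the mortality evaluation need to be reconciled. The primary analysis is not affected.

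**What to change.** 1. **For the whole study.** Reword the safety condition so that a numerical excess in the higher-PEEP group prompts DMC review. Any temporary or permanent stop should follow DMC advice based on the between-group difference and its uncertainty. Refer to the DMC manual for the boundary, which should take account of the three looks and name the outcomes it covers. The choice of boundary is left to the DMC and the sponsor.
2. **Adverse event reporting and harms {22}.** For death, report the risk difference (high minus low PEEP) with its 95% confidence interval alongside the per-group rates. Do the same for the other main safety outcomes.
3. **Link the sections.** Refer each of the two sections, and the DMC section, to the others so that one criterion applies to mortality.

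The cost is two reworded sentences and one entry in the DMC manual, with no extra data and no extra looks. The protocol change goes through the ethics committees in the usual way for amendments.
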